**6.5 Management of other toxicities**

If other Grade < 3 toxicities not listed above occur, give symptomatic treatment whenever possible. If Grade 3 toxicity occurs, withhold the drug treatment. When the toxicity recovers from Grade 3 to Grade ≤ 1, administer the corresponding investigational drug at 85% of the original dose in the next treatment cycle. If Grade 4 toxicity occurs, discontinue all drug treatment. If the toxicity still does not resolve to Grade ≤ 1 four weeks after the start of the next scheduled cycle, the patient should withdraw from the treatment and be followed up according to the protocol until the toxicity is resolved.

However, in the event of certain Grade ≥ 3 adverse events (e.g., when a patient develops symptoms of fatigue, sexual function changes, and clinically insignificant dry skin), the investigator may also decide to allow the patient to continue treatment.

For the second occurrence of non-hematological toxicity, the following dose adjustment methods should be used:

If the patient experiences Grade 3 toxicity again, although the dose of the investigational drug has been previously adjusted, the study dose can still be adjusted again if the investigator believes that the treatment is in the best interest of the patient (otherwise the treatment should be stopped). Adjust the second dose to 70% of the original dose. However, for the second occurrence of Grade 4 toxicity, the above principles do not apply, and the patient should discontinue treatment in this case. If the dose has already been reduced, it cannot be increased thereafter.

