**3.2 Exclusion criteria**

Patients who meet any of the following criteria will be excluded from the study:

- Presence of any extrahepatic metastasis and/or primary tumor that cannot be resected with radical surgery.
- Serious arterial embolism or ascites.
- Have bleeding tendency or coagulation disorder.
- Have hypertensive risk or hypertensive encephalopathy.
- Serious uncontrolled systemic complications such as infection or diabetes.
- Clinically significant cardiovascular disease such as cerebrovascular accident (within 6 months prior to enrollment), myocardial infarction (within 6 months prior to enrollment), uncontrolled hypertension despite appropriate medical treatment. Unstable angina, congestive heart failure (NYHA class 2-4), cardiac arrhythmia requiring medication.
- History or physical evidence of central nervous system disease (e.g., primary brain tumor, epilepsy uncontrolled by standard of care, any history of brain metastases or stroke).
- History of other malignancies (except basal cell carcinoma of the skin and/or carcinoma in situ of the cervix after radical surgery) within the past 5 years.
- Treatment with any ongoing investigational drug within the last 28 days prior to the study.
- Any residual toxicity from prior chemotherapy (except alopecia), such as peripheral neuropathy ≥ NCI CTC v4.03 Grade 2, will not be considered for oxaliplatin-containing regimen.
- Hypersensitivity to any drug in the study.
- Pregnant and lactating women.
- Women of childbearing age (< 2 years after menstruation) or men of childbearing potential who are not using or refuse to use effective non-hormonal contraception (intrauterine contraceptive ring, barrier contraceptives combined with spermicidal gel, or surgical sterilization).
- Unable or unwilling to comply with the study protocol.
- Patients with any other diseases, dysfunction caused by metastatic lesions, or suspected disease found by physical examination, indicating possible contraindications to the use of the investigational drug or putting the patients at high risk of treatment-related complications.

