**6.2 Dose modifications due to hematologic toxicity**

Dose modifications during this or subsequent cycles due to DLT are made as follows:

- For Grade 3 ANC decreased, dose modification of investigational drugs (oxaliplatin/irinotecan, 5-FU) is not needed. For Grade 3 PLT decreased, febrile Grade 3 ANC decreased, or Grade 4 ANC decreased, adjust the dose of oxaliplatin/irinotecan to 80% of the original dose. For Grade 4 PLT decreased or febrile Grade 4 ANC decreased, adjust the dose of oxaliplatin/irinotecan to 70% of the original dose.
- After a dose reduction, if the same or higher grade of toxicity recurs, further reduce the dose of oxaliplatin/irinotecan to 60%. If Grade 4 toxicity persists despite dose modification for Grade 4 toxicity, discontinue oxaliplatin/irinotecan and continue the treatment with cetuximab or FU/CF chemotherapy.
- After the second dose reduction, if the same or higher grade of toxicity recurs, discontinue oxaliplatin/irinotecan and continue the treatment with cetuximab or FU/CF chemotherapy.

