**6.3 Dose modifications due to non-hematologic toxicity**

If the non-hematological toxicity is not clearly related to a certain investigational drug, consider adjusting the dose of all drugs that may cause the adverse reactions; if the non-hematological toxicity is clearly related to a certain investigational drug, consider only adjusting the dose of this drug, while the dose of other investigational drugs may not be adjusted.

Dose adjustment for the first occurrence of non-hematological toxicity:

- Diarrhea
- If diarrhea occurs at any time, the patient must recover to less than Grade 1 diarrhea before restarting treatment. For Grade 1 diarrhea, administer the investigational drug at the original dose; for Grade 2 diarrhea, administer irinotecan and 5-FU at 85% of the original dose; after a dose reduction, if the same or higher grade of toxicity recurs, further reduce irinotecan and 5-FU to 75% of the original dose. For Grade 3 diarrhea, administer irinotecan and 5-FU at 75% of the original dose; after dose reduction, if the same or higher grade of toxicity recurs, further reduce irinotecan and 5-FU to 60% of the original dose. If the patient presents with the following conditions, including Grade 4 diarrhea, diarrhea with fever, and diarrhea with Grade 3 to 4 granulocytopenia, administer irinotecan and 5-FU at 60% of the original dose. After dose reduction, discontinue the treatment if the same or higher grade of toxicity recurs.
- Bilirubin increased

Once bilirubin increased occurs, it is recommended to rule out bilirubin increased caused by biliary obstruction and tumor progression. If bilirubin is > 1.5 × ULN, irinotecan is no longer recommended.

- Transaminases increased

In this study, if the transaminases level is abnormal, it is recommended to rule out transaminase increased caused by tumor progression. Drug treatment will be withheld until toxicity recovers to baseline or ≤ Grade 1 before treatment can be restarted. For Grade 1 and 2 transaminases increased, no dose adjustment is made; for Grade 3 transaminase increased, adjust the dose of oxaliplatin/irinotecan to 80% of the original dose. For Grade 4 transaminases increased, discontinue all treatment. Once a dose reduction has been made due to hepatic function, no further dose reduction is recommended if no worsening of indicators is observed.

- Stomatitis

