If stomatitis occurs at any time, the patient must recover to less than Grade 1 stomatitis before restarting treatment. Dose reduction is required as follows: for Grade 1 stomatitis, administer the investigational drug at the original dose; for Grade 2 stomatitis, administer 5-FU at 85% of the original dose; for Grade 3 stomatitis, administer 5-FU at 70% of the original dose; for Grade 4 stomatitis, discontinue all treatment.

- Cardiotoxicity

Once angina pectoris or myocardial infarction occurs, discontinue 5-FU treatment permanently.

- Hand-foot syndrome:

For Grade 3 or 4 toxicity, withhold the drug treatment until the toxicity recovers to Grade ≤ 1 before restarting the treatment. Dose reduction is required as follows: for Grade 3 hand-foot syndrome, administer 5-FU at 75% of the original dose; for Grade 4 hand-foot syndrome, administer 5-FU at 60% of the original dose.

- Neurotoxicity

For Grade 3 or 4 neurotoxicity, withhold the drug treatment until the neurotoxicity recovers to Grade ≤ 1 before restarting the treatment. Dose reduction is required as follows: for Grade 2 neurotoxicity, administer oxaliplatin at 85% of the original dose; for patients with Grade 3/4 neurotoxicity, discontinue oxaliplatin treatment and patients in the cetuximab plus FOLFOXIRI group may continue to receive either cetuximab or FU/CF chemotherapy.

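### Section 6 has no stop rule for Grade 3 anaphylaxis to oxaliplatin, irinotecan or 5-FU; on the natural reading, the residual rule in 6.5 restarts the drug at 85%

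*Protocol*

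**What the plan says.** Protocol Section 6.5 deals with toxicities not handled earlier in Section 6. For a first Grade 3 event it says: "If Grade 3 toxicity occurs, withhold the drug treatment". After recovery to Grade 1 or less it says to "administer the corresponding investigational drug at 85% of the original dose in the next treatment cycle". For Grade 4: "If Grade 4 toxicity occurs, discontinue all drug treatment". For a repeat Grade 3 event, a further reduction is possible if the investigator thinks treatment is in the "best interest of the patient (otherwise the treatment should be stopped). Adjust the second dose to 70% of the original dose".

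The term investigational drug includes the chemotherapy agents. Section 6.2 uses it that way for Grade 3 neutropenia: "dose modification of investigational drugs (oxaliplatin/irinotecan, 5-FU) is not needed".

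Section 6.4 is headed as covering adverse reactions due to cetuximab. It orders immediate and permanent discontinuation after severe infusion reactions and names anaphylaxis among them. Section 3.2 excludes from entry anyone with "Hypersensitivity to any drug in the study". Section 9.4 lets the investigator stop study drug for any patient at any time, including for a medical event that endangers the patient.

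**The concern.** Rechallenge after anaphylaxis is a different decision from rechallenge after a dose-related toxicity such as diarrhea. The protocol recognises this for cetuximab, where a severe reaction ends treatment with the drug, and at entry, where known hypersensitivity to any study drug is a bar. It also gives allergic bronchospasm needing emergency rescue as an example of a serious adverse event in Section 11.1. For the three chemotherapy drugs, however, the only dosing instruction that reaches the event is a percentage reduction. A site following Section 6 literally would re-expose a patient who has just had bronchospasm, angioedema or hypotension from the drug. What is at stake is the safety of the few patients concerned, not the validity of the primary comparison.

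**Working it through.** No sample-size or error-rate figure is involved. The check sets the relevant sections side by side and then applies the stated percentages to the stated doses.

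**Step 1: is there a specific rule for chemotherapy allergy?**

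| Section | Covers | Allergy rule for oxaliplatin, irinotecan or 5-FU? |
|---|---|---|
| 6.1 | General principles; conditions for starting each cycle | No |
| 6.2 | Neutrophils and platelets | No |
| 6.3 | Diarrhea, bilirubin, transaminases, stomatitis, cardiotoxicity, hand-foot syndrome, neurotoxicity | No |
| 6.4 | Cetuximab: infusion reactions including anaphylaxis; skin reactions | No (cetuximab only) |
| 6.5 | Other toxicities | Not by name; residual Grade 3 and Grade 4 rules |
| 6.6 | Concomitant drugs; diphenhydramine before cetuximab to prevent anaphylaxis | No rule for after an event |

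Where the authors wanted a rule for a specific chemotherapy toxicity, they wrote it in 6.3. Examples are "For Grade 3 diarrhea, administer irinotecan and 5-FU at 75% of the original dose", a permanent stop of 5-FU after angina or infarction, and, for Grade 3/4 neurotoxicity, "discontinue oxaliplatin treatment and patients in the cetuximab plus FOLFOXIRI group may continue to receive either cetuximab or FU/CF chemotherapy". Hypersensitivity is not on that list.

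**Step 2: where does a Grade 3 anaphylaxis to chemotherapy go?** With no entry in 6.2 or 6.3, and 6.4 confined to cetuximab, the section left is 6.5. Its first-event sequence is to withhold, wait for Grade 1 or less, then give the causative drug at 85%.

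**Step 3: does the recovery condition protect the patient?** Hardly. In Appendix III anaphylaxis has no Grade 1 or Grade 2; its lowest grade is 3 (symptomatic bronchospasm, allergy-related edema, hypotension). Once the acute event is over, the condition for restarting is met. The earliest restart is the next 14-day cycle.

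**Step 4: what doses follow?** Starting doses are from Section 5.2, in mg/m². Irinotecan is shown at each level that the 3+3 scheme can reach.

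| Drug | Start | × 0.85 (first event) | × 0.70 (second event, conditional) |
|---|---|---|---|
| Oxaliplatin | 85 | 72.25 | 59.5 |
| Irinotecan | 100 | 85 | 70 |
| Irinotecan | 130 | 110.5 | 91 |
| Irinotecan | 150 | 127.5 | 105 |
| 5-FU bolus (mFOLFOX6 arm only) | 400 | 340 | 280 |
| 5-FU infusion | 2400 | 2040 | 1680 |

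These figures show what the rule would produce. They do not measure harm.

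**Step 5: how many patients could be affected?** Section 4 plans 140 patients, 70 per arm. Both regimens contain oxaliplatin and 5-FU, so all 140 are assigned those drugs; the 70 in the FOLFOXIRI arm are also assigned irinotecan. The protocol states no incidence of Grade 3 anaphylaxis to these drugs. At an assumed 1%, 0.01 × 140 = 1.4 patients; at an assumed 5%, 0.05 × 140 = 7 patients. The range has no anchor in the document.

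**The case against.** **Section 6.5 does not name anaphylaxis.** Its opening sentence concerns lower-grade toxicities not covered earlier, and anaphylaxis is discussed earlier, in 6.4. A reader could hold that 6.5 was never meant for it. This stands as an alternative reading: 6.5 reaches the event by inference. It does not remove the problem, because 6.4 discusses anaphylaxis only as a cetuximab reaction. On that reading chemotherapy anaphylaxis has no rule in Section 6, which is still not a stop.

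**The investigator can already stop.** Section 9.4 gives that right at any time, and bronchospasm or hypotension is plainly an event that endangers the patient. Section 11.4.1 lists permanent discontinuation among the recordable actions. All of this stands, so a reader who infers that the protocol compels re-exposure goes too far. But 9.4 is general discretion, while 6.5 is a specific dosing instruction. The discretion written into 6.5 for selected Grade 3 or higher events works toward continuing treatment.

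**Section 6.4 is not a uniform model.** For a reaction within 15 minutes of the first cetuximab dose, it asks for a risk-benefit assessment before later infusions, with no grade attached. The graded list that ends treatment at Grade 3 and 4 is introduced for reactions late in the infusion or at later infusions. The general sentence on severe reactions does say permanent, so the contrast with chemotherapy survives, in less clean form.

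**Premedication.** Diphenhydramine is given before cetuximab, and all drugs start on day 1, so it may give some cover for the chemotherapy too. That bears on prevention, not on what to do after an event.

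**Conclusion.** The point holds in a narrow form: first event, Grade 3, recovered, caused by oxaliplatin, irinotecan or 5-FU. For that event Section 6 gives either an instruction to restart at 85% (the natural reading) or no rule (the alternative reading), and stopping depends on 9.4 alone. Grade 4 is already a full stop, and the 70% dose after a second event depends on the investigator's judgement.

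Three stronger conclusions might be drawn, and the document does not support them:

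- That 6.5 overrides every Grade 3 rule before it. It is a residual rule; the specific rules for diarrhea, neurotoxicity and the others in 6.2 to 6.4 stand.
- That stopping one drug would leave only cetuximab or FU/CF to continue. Section 6.3 already allows the other drugs to go on unadjusted when one drug is clearly the cause, and its narrower wording belongs to Grade 3/4 neurotoxicity.
- That the trial's results are affected. No effect on ORR or error rates is shown or claimed.

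The finding is a cheap patient-safety improvement of minor weight. It rests on taking the heading of 6.4 at face value. The statement that no chemotherapy rule exists is made for Sections 6.1 to 6.6, which were read in full; the text that follows 11.4.1 was not available for this check.

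**What to change.** Add two sentences to Section 6.5:

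> Grade 3 anaphylaxis attributed to any study drug is exempt from the 85%/70% adjustments: permanently discontinue that drug. For other Grade 3 allergic reactions, re-exposure requires a documented investigator risk-benefit decision.

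The Grade 4 sentence stays as it is, and 6.4 continues to govern cetuximab. No sentence on continuing the other drugs is needed.

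The cost is a short protocol amendment and one documented decision for each non-anaphylactic Grade 3 allergic reaction. No extra patients, tests or staff are required, and the sample size does not change. The downside is that a few patients lose reduced-dose re-exposure to one drug.

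### Section 6.5's 70% dose for a repeat Grade 3 non-hematological event gives no reduction for recurrent stomatitis and differs from 6.3's 60% for recurrent diarrhea

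*Protocol*

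**What the plan says.** Section 6.3 introduces its list of toxicities with "Dose adjustment for the first occurrence of non-hematological toxicity". Two entries matter here.

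- Diarrhea: a first Grade 3 event takes irinotecan and 5-FU to 75% of the original dose. A recurrence has its own step: "after dose reduction, if the same or higher grade of toxicity recurs, further reduce irinotecan and 5-FU to 60% of the original dose". Grade 4 diarrhea, and diarrhea with fever or with Grade 3 to 4 granulocytopenia, go straight to 60%, and treatment stops if they recur.
- Stomatitis: Grade 3 takes 5-FU to 70%, and Grade 4 stops all treatment. The patient must be below Grade 1 before restarting. Nothing is said about a second Grade 3 event.

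Section 6.5 is titled as covering other toxicities and opens with those not listed before it. An unlisted Grade 3 event goes to 85%. A later paragraph is introduced more broadly: "For the second occurrence of non-hematological toxicity, the following dose adjustment methods should be used". For a repeat Grade 3 event after an earlier adjustment its single figure is "Adjust the second dose to 70% of the original dose". That figure applies "if the investigator believes that the treatment is in the best interest of the patient (otherwise the treatment should be stopped", so stopping is the stated alternative.

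**The concern.** The introductory lines of 6.3 and 6.5 read as a matched pair: first occurrence, then second occurrence, of non-hematological toxicity. The second line exempts none of the toxicities that 6.3 lists, and no sentence says which section prevails. Taken as worded, the 70% figure therefore reaches stomatitis and diarrhea.

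The stomatitis case is the main defect. A second Grade 3 event at 70% of the original 5-FU dose is met by a rule that speaks of adjusting the dose again, yet the figure it gives is the dose at which the event came back. For diarrhea the two sections simply name different doses. What is at stake is patient safety at the bedside. The wording has no bearing on the sample size, the type 1 error or the ORR comparison.

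**Working it through.** There is no calculated figure in the plan to reproduce. The check is to follow each toxicity from its first to its second Grade 3 event.

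**Inputs.** Section 5.2: irinotecan starts at 130 mg/m2 (150 if escalated); infusional 5-FU is 2400 mg/m2. Section 6.3, first Grade 3 event: diarrhea 75% (irinotecan and 5-FU), stomatitis 70% (5-FU), hand-foot syndrome 75% (5-FU). Section 6.3, recurrent Grade 3 diarrhea: 60%. Section 6.5: unlisted toxicity 85% at the first Grade 3 event; repeat Grade 3 event 70%.

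**Relative cut at the second Grade 3 event** = (current % − new %) / current %.

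| Toxicity | Current | New, by 6.5 | Cut by 6.5 | Cut by 6.3's own step |
|---|---|---|---|---|
| Stomatitis | 70% | 70% | (70 − 70)/70 = 0% | none given |
| Diarrhea, uncomplicated | 75% | 70% | (75 − 70)/75 = 6.7% | (75 − 60)/75 = 20.0% |
| Hand-foot syndrome | 75% | 70% | (75 − 70)/75 = 6.7% | none given |
| Unlisted | 85% | 70% | (85 − 70)/85 = 17.6% | not applicable |

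**Doses, recurrent Grade 3 stomatitis.** Infusional 5-FU before: 0.70 × 2400 = 1680 mg/m2. After, by 6.5: 0.70 × 2400 = 1680 mg/m2. No change.

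**Doses, recurrent uncomplicated Grade 3 diarrhea.**

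- Irinotecan from 130: 0.60 × 130 = 78 mg/m2 by 6.3; 0.70 × 130 = 91 mg/m2 by 6.5.
- Irinotecan from 150: 0.60 × 150 = 90 mg/m2; 0.70 × 150 = 105 mg/m2.
- Infusional 5-FU: 0.60 × 2400 = 1440 mg/m2; 0.70 × 2400 = 1680 mg/m2.
- The 6.5 dose is 0.70/0.60 − 1 = 16.7% higher than the 6.3 dose, though still below the 75% the patient was receiving.

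**The narrower reading.** If the repeat-event paragraph of 6.5 is confined to unlisted toxicities, 85% then 70% is a coherent ladder and the diarrhea mismatch disappears. Recurrent Grade 3 stomatitis then has no dose rule in either section, and neither does recurrent Grade 3 hand-foot syndrome. Stomatitis is therefore unresolved on both readings.

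**The case against.** The strongest reply is that there is no true contradiction for diarrhea. Section 6.3 gives diarrhea its own ladder, 6.5 is by title and opening a residual section, and a specific rule ordinarily governs over a residual one. That largely stands: most investigators would use 60%. A reader might infer that patients with recurrent Grade 3 diarrhea would in practice be given the higher dose; the text does not support that.

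On stomatitis, the reply is that nothing compels re-exposure. Section 6.5 makes continuing a matter of judgment, 6.3 requires recovery to below Grade 1 first, and section 9.4 lets the investigator discontinue at any time. This limits the harm, but it does not supply a lower dose for the patient who does continue.

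A reader might also take 6.5's sentence on a repeat Grade 4 event ("However, for the second occurrence of Grade 4 toxicity, the above principles do not apply, and the patient should discontinue treatment in this case") as proof that the paragraph was written for 6.3's toxicities, because 6.5 already says "If Grade 4 toxicity occurs, discontinue all drug treatment" of unlisted ones. The inference is weak. Section 6.3 itself stops Grade 4 diarrhea that recurs after reduction, and Appendix III lists no Grade 4 for palmar-plantar erythrodysesthesia. A repeat Grade 4 unlisted event can also arise under 6.5's discretionary exception, where "the investigator may also decide to allow the patient to continue treatment". The point rests on the paired introductory lines and the missing exemption.

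Lastly, a count of affected patients is tempting. Section 1 cites 25% Grade 3/4 diarrhea in one earlier study of cetuximab plus a triplet, and 0.25 × 70 = 17.5 first events in the triplet arm. The documents do not support going further. They give no recurrence rate. The 25% includes Grade 4 events, and any febrile or granulocytopenic cases in it would, like Grade 4, go straight to 60% here and never meet the mismatch. Section 11.2 also expects serious gastrointestinal reactions to be relatively rare.

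**Conclusion.** The point holds as a minor patient-safety clarification. For recurrent Grade 3 stomatitis the protocol offers either an unchanged 5-FU dose or, on the narrower reading, no rule. The alternative it states in 6.5 is to stop. For recurrent uncomplicated Grade 3 diarrhea the sections as worded differ by 10 percentage points of the original dose, with 60% the likelier choice in practice.

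The stomatitis conclusion does not depend on how the scope of 6.5 is read; the diarrhea mismatch does, since it requires the repeat-event paragraph to cover toxicities listed in 6.3. No effect on ORR follows, and the number of patients concerned cannot be derived from the documents.

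**What to change.** Amend sections 6.3 and 6.5 to say three things.

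1. Recurrence steps that 6.3 gives for a particular toxicity take precedence, so recurrent Grade 3 diarrhea goes to 60%.
2. The 70% in 6.5 applies only where 6.3 has no recurrence step and the current dose is above 70%, for example hand-foot syndrome from 75% or an unlisted toxicity from 85%.
3. Recurrent Grade 3 stomatitis, or any repeat Grade 3 event at or below 70% without its own step, leads to a lower dose (for example 60%) or to stopping the causative drug.

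The cost is a few sentences in an amendment, with no added patients, visits or procedures. The choice between 60% and stopping for stomatitis is clinical and belongs to the investigators.
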